## Statistical methods

### Statistical methods for primary and secondary outcomes {20a}

Patient characteristics at the time of randomisation will be summarised using mean and SD for continuous variables which are approximately normally distributed, median and interquartile range (IQR) for variables which are not normally distributed, or by frequencies and percentages for categorical variables. All statistical hypothesis tests will use a two-sided *p* value of 0.05 unless otherwise specified. All confidence intervals (CIs) presented will be 95% and two-sided. All statistical analysis will be performed using Stata (StataCorp, College Station, TX, USA) or an alternative package.

#### Primary outcome

The primary outcome is the difference between the intervention group and the control group in the total difficulties score of the parent-reported SDQ at 6 months post-randomisation.

The total difficulties score of the SDQ has a range of 0–40. Mixed effect linear regression will be used to determine if there is any difference in the total difficulties score due to intervention. The model will include fixed effects for intervention group, baseline SDQ total difficulties score and the stratification factors; age (< 11 versus 11+), primary mental health disorder (anxiety, depression, disruptive behaviour or trauma), presence of autistic spectrum disorder (yes/no) and presence of intellectual disability (yes/no). A random factor, *Therapist*, will be included to take account of therapist effects. Results will be presented as adjusted treatment effect and the associated 95% CI. If the intervention is effective, we would expect to see a reduction in the total difficulties score (higher total difficulties score indicates a higher risk of a diagnosis of mental illness).

The primary analysis will be conducted following the intention-to-treat principle in accordance with the randomised intervention. All efforts will be made to ensure that the primary outcome data is collected for all patients, whether or not they complete their randomised treatment. Missing baseline data are not anticipated since baseline data are completed prior to randomisation and must be recorded to allocate treatment. All patients with reported outcome data will be included in the analysis. The primary analysis is likelihood based and therefore robust to the assumption of missing-at-random, but should substantial missing data be encountered, reasons for missingness will be explored and a sensitivity analysis will be undertaken to investigate the validity of the missing at random assumption.

#### Secondary outcomes

Separate analyses will be performed for outcomes at 6 months and at 12 months.

The timing of the primary effectiveness outcome at 6 months is because we expect to see the maximum benefit of treatment at this time point. However, we will be following up the children and the difference at 12 months is a secondary outcome.

Models for all secondary efficacy outcomes will be adjusted for the stratification factors.

Binary secondary outcomes will be analysed using mixed effects logistic regression, ordinal secondary outcomes with mixed effects ordinal logistic regression, and continuous secondary outcomes with mixed effects linear regression.

Fisher’s exact test will be used to compare the proportion of children with any serious adverse events in the two randomised groups.

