**Methods:**

In total, 334 participants aged 3–18 years attending epilepsy services will be screened for mental health disorders with the Strengths and Difficulties Questionnaire (SDQ) and the diagnostic Development and Wellbeing Assessment (DAWBA). Those identified as having a mental health disorder and consenting to the trial will be randomised to either receive up to 22 sessions of the modular psychological intervention (MATCH-ADTC) delivered over the telephone over 6 months by non-mental health professionals in addition to usual care or to assessment-enhanced usual care alone. Outcomes will be measured at baseline, 6 months and 12 months post-randomisation. It is hypothesised that MATCH-ADTC plus usual care will be superior to assessment-enhanced usual care in improving emotional and behavioural symptoms. The primary outcome is the SDQ reported by parents at 6 months. Secondary outcomes include parent-reported mental health measures such as the Revised Children’s Anxiety and Depression Scale, quality of life measures such as the Paediatric Quality of Life Inventory and physical health measures such as the Hague Seizure Severity Scale. Outcome assessors will be blinded to group assignment. Qualitative process evaluations and a health economic evaluation will also be completed.

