### Outcomes {12}

#### Primary outcome

The primary outcome measure is the total difficulties score from the Strengths and Difficulties Questionnaire (SDQ) [25, 26] reported by the parent/carer at 6 months post-randomisation. The SDQ is a brief behavioural screening questionnaire for children and young people aged 2 years and above. The 25 items are divided between 5 scales (emotional, conduct problems, hyperactivity/inattention, peer relationship problems, prosocial behaviour), with the first four added to provide a total difficulties score. The SDQ has good internal consistency (mean Cronbach *α* .73), cross-informant correlation (mean 0.34), and retest stability after 4 to 6 months (mean 0.62) [30]. SDQ scores above the 90th percentile predict a substantially raised probability of independently diagnosed psychiatric disorders (mean odds ratio 15.7 for parent scales) [30]. It has been validated across the age range of children and young people seen within neurology clinics and used in those with autism spectrum disorder [31] and intellectual disabilities [32] known to be highly prevalent in this group [33]. Further, the SDQ has an ‘impact scale’, which assesses the impact that symptoms have on everyday life in a range of domains (home, school, leisure). The parent-reported measure was chosen for data completeness, as the self-report version is unsuitable for young people under the age of 11 years.

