### Sample size {14}

The sample size is 334 children and young people with epilepsy, and their parents /carers.

Previous effect size (ES; standardised magnitude of the effect) estimates for MATCH-ADTC using measures comparable to the SDQ range from 0.51 to 0.65 [14, 15]. Previous published research has estimated the ES for usual care in UK CAMHS to be 0.16–0.2 [47]. We have therefore conservatively based our calculation on an ES = 0.3 which is modest for a psychological intervention study. Our small pilot study comparing the guided self-help psychological intervention against a waitlist control found a large effect size.

A total sample size of 334 children has been chosen as this could detect an effect size of 0.3 for the SDQ, at the 5% significance level with 80% power, assuming an average of 14 children per therapist, an intraclass correlation coefficient (ICC) of 0.01 for therapist effects, a correlation of 0.5 between baseline and follow-up SDQ, and a loss to follow-up rate of 10%. We will take steps to minimise the amount of missing data. A generalised mixed model will be used to analyse the primary outcome adjusting for baseline SDQ and minimisation variables.

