Cost-effectiveness will be assessed using the net benefit approach and following standard approaches [50]. A joint distribution of incremental mean costs and effects for the two groups will be generated using nonparametric bootstrapping to explore the probability that each of the treatments is the optimal choice, subject to a range of possible maximum values (ceiling ratio) that a decision-maker might be willing to pay for an additional unit of outcome gained. Cost-effectiveness acceptability curves will be presented by plotting these probabilities for a range of possible values of the ceiling ratio [51]. These curves are a recommended decision-making approach to dealing with the uncertainty that exists around the estimates of expected costs and expected effects associated with the interventions under investigation and uncertainty regarding the maximum cost-effectiveness ratio that a decision-maker would consider acceptable.

All economic analyses will be adjusted for co-variates in line with the clinical analyses described above, including the stratification variables (age (< 11 versus 11+), primary mental health disorder (anxiety, depression, disruptive behaviour or trauma), presence of autistic spectrum disorder (yes/no), presence of intellectual disability (yes/no) and for the baseline values of the variables of interest (e.g. baseline cost, CHU-9D score, as appropriate).

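### The covariate rule for the secondary efficacy models names the stratification factors but not the outcome's baseline value, unlike the primary and economic models

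*Protocol article*

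**What the plan says.** In the protocol article, Statistical methods {20a}, the Secondary outcomes paragraph gives one covariate rule: "Models for all secondary efficacy outcomes will be adjusted for the stratification factors". The same paragraph places the later SDQ under this rule: "we will be following up the children and the difference at 12 months is a secondary outcome".

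Three other places bear on it.

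- Statistical methods {20a}, Primary outcome: "The model will include fixed effects for intervention group, baseline SDQ total difficulties score and the stratification factors". Baseline score and stratification factors are separate items.
- Economic analysis: the models adjust for the stratification variables "and for the baseline values of the variables of interest". Again the two are listed separately.
- Abstract, Methods: "Outcomes will be measured at baseline, 6 months and 12 months post-randomisation".

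The stratification factors, listed under Sequence generation {16a}, are primary disorder, autism, age group and intellectual disability. None is a symptom score, so adjusting for them does not bring a baseline score in.

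**The concern.** The secondary rule gives a shorter covariate list than the models on either side of it, although the baseline data should be in hand. Three things are at stake if it is followed literally.

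- **Comparability over time.** Trial design {8} says the measures are repeated at one year to see whether improvement lasts. The 6-month SDQ effect would be baseline-adjusted and the 12-month effect would not. An apparent fading of the effect, or a loss of significance, could partly reflect the change of model.
- **Two answers to one question.** The primary economic analysis is set at 12 months and uses the SDQ total difficulties score. Its covariate rule includes baseline values. The clinical 12-month SDQ analysis, as written, does not, so the same contrast could be reported with two different estimates.
- **Precision.** RCADS, PHQ-9, GAD-7, HASS, PedsQL and the 12-month SDQ would have wider intervals than the collected data allow.

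**Working it through.** **Inputs.** All are from Sample size {14} unless noted: effect size 0.3 SD; 5% significance, two-sided (Statistical methods {20a}); power 80%; 14 children per therapist; ICC 0.01; "a correlation of 0.5 between baseline and follow-up SDQ, and a loss to follow-up rate of 10" per cent; allocation 1:1 (Sequence generation {16a}).

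**Step 1: reproduce the 334.**

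- Unadjusted n per arm: 2 × (1.96 + 0.8416)² / 0.3² = 174.4, rounded up to 175.
- Baseline adjustment: 175 × (1 − 0.5²) = 175 × 0.75 = 131.25, rounded up to 132.
- Design effect 1 + (14 − 1) × 0.01 = 1.13: 132 × 1.13 = 149.2, rounded up to 150.
- Loss to follow-up: 150 / 0.9 = 166.7, rounded up to 167 per arm, **334 in total**.

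This matches exactly. Without the factor 0.75 the same chain gives 175 × 1.13 = 197.75, rounded up to 198; 198 / 0.9 = 220 per arm; 440 in total. The design of the primary comparison therefore relies on baseline adjustment.

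**Step 2: the SDQ without its baseline.** Analysed per arm: 334 × 0.9 / 2 = 150.3. Effective number: 150.3 / 1.13 = 133.0.

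- Standard error with baseline: √(0.75 × 2 / 133.0) = 0.106 SD.
- Standard error without baseline: √(2 / 133.0) = 0.123 SD.
- Ratio: 1 / √0.75 = 1.155, so the confidence interval is about 15% wider and the variance 33% larger (1 / 0.75 = 1.33).
- Information lost: r² = 0.5² = 25%.

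For illustration, power for a 0.3 SD difference is Φ(0.3 / 0.106 − 1.96) = 80.6% with baseline and Φ(0.3 / 0.123 − 1.96) = 68.7% without (unrounded standard errors used).

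**Step 3: the other scales.** The protocol gives no baseline-to-follow-up correlation for them, so r is an assumption and a range is shown. The design effect cancels in these ratios.

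| r | Information lost (r²) | Interval width ratio, 1/√(1 − r²) |
|---|---|---|
| 0.2 | 4% | 1.02 |
| 0.3 | 9% | 1.05 |
| 0.4 | 16% | 1.09 |
| 0.5 (SDQ, sample size section) | 25% | 1.15 |
| 0.62 (SDQ retest stability, Outcomes {12}) | 38% | 1.27 |
| 0.7 | 49% | 1.40 |

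**Step 4: what these figures leave out.** They compare baseline adjustment with no adjustment at all, but the strata stay in the secondary models. Where the strata explain some of the same outcome variance as the baseline score, the net loss is smaller than r². The documents give no figure for that overlap.

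**The case against.** The strongest reply is that this is silence, not a decision. The sentence does not say that the strata are the sole covariates, and it does not exclude baseline. It is compressed in other ways too: it does not restate the treatment term, and nobody would conclude that treatment is left out. The article condenses a longer protocol, and the unseen SAP may well add baseline. The economic section also describes its covariates as consistent with the clinical analyses, which hints that strata plus baseline is the general pattern. This part stands: a reader might infer that the trial has chosen to discard its baseline data, and the text does not support that.

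It does not dispose of the point. Elsewhere the article says openly when it leaves a matter to the SAP, as for mediators and moderators {20b} and multiple imputation {20c}. Here it states a rule for all secondary efficacy outcomes, and that rule is shorter than its two neighbours. The economic wording could refer to the primary model alone, so it does not settle the matter.

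Four further objections hold in part.

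- The correlation of 0.5 is for the SDQ and is not tied to 12 months. Carrying a loss of one quarter over to every secondary outcome is not supported.
- The protocol claims no power for any secondary outcome, so the fall from 80.6% to 68.7% misses no stated target.
- Primary disorder plausibly overlaps with baseline RCADS and may already absorb part of the gain.
- Baseline measurement of each scale rests on the general statement in the abstract. The schedule by measure is in a table not reproduced in the text available, hence the qualifier on measurement in the proposed change.

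**Conclusion.** The point stands as a gap in a stated rule. As written, the secondary models carry a smaller covariate set than the primary and economic models, and the 12-month SDQ would not be analysed like for like with the 6-month SDQ.

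For the SDQ the loss is up to 25% of the information (interval about 15% wider). This assumes that r = 0.5 also holds at 12 months, and it is reduced by whatever the strata already explain. For the other scales it is about r², from 4% to 49% over assumed correlations of 0.2 to 0.7.

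A reader might go further and infer bias from chance baseline imbalance. Allocation is randomised, so the unadjusted estimates are unbiased and their intervals already allow for such imbalance; it is the same loss of precision seen from another side. A reader might also infer that the trial is underpowered. It is not on this account: the primary model does adjust for baseline, and the 334 is reproduced with that adjustment.

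**What to change.** Replace the sentence in the Secondary outcomes paragraph of Statistical methods {20a} with wording such as: *Each secondary efficacy model, including that for the SDQ at 12 months, will contain the baseline value of the outcome being analysed, where it was measured, together with the stratification factors.*

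If the SAP already says this, the protocol sentence should be brought into line with it. The change is one sentence and uses baseline data that the abstract says are collected. It aligns the secondary models with the primary and economic ones. Made before results by arm are seen, it also removes a discretionary choice of covariates.

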#### Secondary outcomes

Revised Child Anxiety and Depression Scale (RCADS) [34]. This 47-item questionnaire is one of the main outcome measures used in the Children and Young People’s Improving Access to Psychological Therapies (CYP-IAPT) Programme. It is included to allow comparison with this national initiative and has parent and child versions, the subscales are reliable (Cronbach *α* .78–.88) and the measure has discriminant, convergent and factorial validity in a clinical sample [35]. For the trial, the parent version will be used for data completeness.Patient Health Questionnaire (PHQ-9) [36]. This is a 9-item measure of depression in adults completed by the parent/carer about their own mental health.Generalised Anxiety Disorder Assessment (GAD-7) [37]. This is a 7-item measure of generalised anxiety disorder, completed by the parent/carer about their own mental health.Hague Seizure Severity Scale (HASS) [38]—this is a parent-report questionnaire which rates carers’ subjective experiences of the severity of their child’s seizures. Items are statements, which are rated on a 4-point scale from most to least severe (e.g. ‘always’, ‘usually’, ‘sometimes’ or ‘never’). Items describe the length, type and outcomes of a seizure—for example ‘how long do the jerks or cramps last during an attack?’Paediatric Quality of Life Epilepsy Module (PedsQL) [39]. The PedsQL measures the impact of epilepsy on quality of life.Number of serious adverse events. Serious adverse events are those that result in death, are life threatening, require hospitalisation or prolong existing hospitalisation, result in persistent or significant disability or incapacity, or result in a congenital anomaly or birth defect or another important medical condition.

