### Adverse event reporting and harms {22}

For the purposes of the MICE trial, only serious adverse events will be reported. All serious adverse events (SAEs) occurring during the trial observed by the investigator or reported by the participant, whether or not attributed to the trial treatment will be recorded on the database. Low-grade adverse events that do not meet the seriousness criteria will not be reported, for example a grade 1 or 2 epileptic seizure that does not result in hospitalisation.

Investigators should notify CCTU immediately and within 24 h at the latest of any SAEs occurring from the time of randomisation until 30 days after the participant completes trial treatment. From this point forward, the site will notify the CCTU of SAEs that are considered related to the trial intervention if they become aware of them until end of follow-up.

Participants must be followed up until clinical recovery is complete, or until the event has stabilised. Follow-up should continue after completion of trial treatment and/or trial follow-up if necessary. Follow-up SAE forms (clearly marked as follow-up) should be completed and emailed to CCTU as further information becomes available. Additional information and/or copies of test results, etc., may be provided separately.

Medically qualified staff appointed by the sponsor will review all SAE reports received. The reviewer will complete the assessment of expectedness.

SAEs that are considered to be related to the trial (resulted from administration of any of the research procedures) and unexpected must be reported to the REC and DMEC. If the related and unexpected event is fatal or life threatening, it must be reported within 7 days of becoming aware of the event; other related and unexpected events must be reported within 15 days.

A list of expected occurrences as a result of the trial treatment is as follows:

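### The named safety outcome is a count of serious adverse events, but the only stated analysis compares the proportion of children with any event

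*Protocol article*

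**What the plan says.** In Outcomes {12}, the list of secondary outcomes includes "Number of serious adverse events", with the usual seriousness criteria, hospitalisation among them.

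In Statistical methods {20a}, the paragraph on secondary outcomes assigns models by type of variable: "Binary secondary outcomes will be analysed using mixed effects logistic regression, ordinal secondary outcomes with mixed effects ordinal logistic regression, and continuous secondary outcomes with", where the last type gets a linear mixed model. For SAEs it then states one analysis, Fisher's "exact test will be used to compare the proportion of children with any serious adverse events in the two randomised groups". Tests are two-sided at 0.05.

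Adverse event reporting and harms {22} sets out what goes on the database: "All serious adverse events (SAEs) occurring during the trial observed by the investigator or reported by the participant, whether or not attributed to the trial" intervention. Sites must notify the trials unit of "any SAEs occurring from the time of randomisation until 30 days after the participant completes trial treatment". After that point, sites notify only SAEs considered related to the intervention.

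The article gives no expected SAE rate and no power statement for safety. The planned total is 334, randomised 1:1.

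**The concern.** The outcome is a count per child or per arm, and the test uses a yes/no per child. A child admitted once and a child admitted five times contribute the same to it. Hospitalisation makes an event serious, and the article's own example of an event that need not be reported is a low-grade seizure without admission. Seizure admissions are therefore reportable, and they can recur in the same child.

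Non-serious events are not reported at all, so SAEs are the trial's only adverse-event data. If the intervention changed how often children are admitted rather than how many are ever admitted, the stated comparison would not pick it up. Two unreconciled definitions also leave open which one is presented as the result for this outcome, and that choice should not be made after the data are seen.

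**Working it through.** **Side by side.** The outcome is a number of events. The stated test is on the proportion of children with at least one event. The stated models are logistic, ordinal logistic and linear, with no count or rate model. Every SAE is recorded, so the count can be built. The mismatch follows from the text and needs no arithmetic.

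**Sample size.** The plan's own figure reproduces. An effect of 0.3 at 5% two-sided and 80% power needs 176 per arm (t-based). Multiply by 1 − 0.5² = 0.75 for the baseline correlation: 132. Multiply by 1 + (14 − 1) × 0.01 = 1.13 for therapist clustering: 149.16, rounded up to 150. Divide by 0.9 for 10% loss: 166.7, rounded up to 167 per arm, or 334. This figure was set for the SDQ and says nothing about SAEs. It is used here only for the 167 per arm.

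**What the test cannot see.** Suppose 25 of 167 children in each arm have at least one SAE. Fisher's p is 1.00 whether the event totals are 30 v 30 or 30 v 60. This is an invented case with equal prevalence. It shows what the test leaves out, not what is likely.

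**Size under assumptions.** Assume gamma-Poisson counts with shape k = 0.5, control mean μ events per child, intervention mean 2μ and 167 per arm. The probability of at least one event at mean m is 1 − (k/(k + m))^k. The share of events that are repeats is 1 − [P(any at μ) + P(any at 2μ)]/(3μ).

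Example at μ = 0.3: P(any) = 1 − (0.5/0.8)^0.5 = 0.209 in control and 1 − (0.5/1.1)^0.5 = 0.326 in intervention. The repeat share is 1 − 0.535/0.9 = 0.41.

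Power by simulation, Fisher's test on any event versus a robust comparison of rates:

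| Control events per child (μ) | Repeat share | Fisher | Rate comparison | Gap (points) |
|---|---|---|---|---|
| 0.03 | 7% | 14% | 19% | 5 |
| 0.05 | 11% | 24% | 32% | 8 |
| 0.1 | 19% | 43% | 55% | 12 |
| 0.3 | 41% | 63% | 86% | 23 |
| 0.5 | 52% | 66% | 93% | 27 |

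Repeated runs agree to within about two percentage points. With equal rates, Fisher's test rejects in about 2–4% of trials, below the nominal 5%. Part of each gap is therefore the exact test's conservatism and not the loss of repeat events.

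Dispersion matters too. At μ = 0.1, the figures are 57% v 66% with Poisson counts and 28% v 43% with strong overdispersion (k = 0.2).

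**The case against.** Comparing children with at least one SAE is a standard safety summary. It needs no dispersion model, is not driven by one frequently admitted child, and keeps type I error below 5% when counts are low. If SAEs are rare, little is lost: at 0.03 to 0.05 events per control child both tests are weak and the gap is 5 to 8 points. Safety oversight does not rest on this p-value either, because the data monitoring committee sees accumulating comparative data and every SAE report has medical review. All of this stands, and it is why Fisher's test should be kept.

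A reader might infer that repeat events are thrown away, or that the number of SAEs will never be compared. The documents do not support either. All SAEs go on the database, so repeats are absent only from the stated test. The article is a condensed protocol and the statistical analysis plan is not shown, so event totals or a rate analysis may be specified there.

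What remains is narrower. The article fixes both an outcome and a test, and they do not match. A later plan could resolve this, but the published text would still need to be brought into line.

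It is also fair to object that a rate model is not simply an add-on. Full notification ends 30 days after trial treatment is completed, and the article does not say when that point falls for a child on usual care alone. Person-time under full reporting is therefore not defined in that arm, and the fix has to settle this first.

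**Conclusion.** The point holds as a mismatch between a named outcome and its only stated analysis. An excess of repeat SAEs in one arm would not show in that analysis. The consequence is confined to one safety outcome.

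Its size cannot be fixed from the document. For a true doubling of the rate with shape 0.5, the power given up ranges from about 5 points at 0.03 events per control child to about 27 points at 0.5, partly through Fisher's conservatism. The event rates, the dispersion and the rate ratio are all assumptions. The any-event comparison is not wrong in itself; it answers a different question from the one the outcome list poses.

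**What to change.** Keep Fisher's exact test for children with any SAE. Add the total number of SAEs per arm and a between-arm rate ratio with 95% CI from a method robust to overdispersion (negative binomial, or Poisson with robust variance). Count events over one stated period from randomisation in which all SAEs are reported in both arms. The harms section should define that period without reference to completing trial treatment. The any-event proportion should use the same period.

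If the sponsor does not intend to compare counts, reword the outcome as the proportion of children with at least one SAE and report event totals by arm descriptively.

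The cost is one extra model on events already recorded, plus a clear definition of the common reporting period. The model may be unstable with very few events. State in advance that in that case only the event totals and the exact test will be reported. No change to the sample size or the primary analysis is needed.
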